## Assignment of interventions: blinding

### Who will be blinded {17a}

Trained master students in psychology will be blinded for the treatment condition of the participant, and they will conduct the baseline and follow-up interviews.

### Procedure for unblinding if needed {17b}

Not applicable as participants will be aware about whether they receive TAU or NET.

## Data collection and management

### Plans for assessment and collection of outcomes {18a}

PTSD symptoms will be assessed using the PTSD Symptom Scale Interview for DSM-5 (PSS-I) [24]. The PSS-I-5 assesses for PTSD diagnosis according to the DSM-5 [34]. Scores for each item range from 0 (not at all) to 4 (≤ 6 times a week/severe). Diagnosis will be ascertained according to the manual, and sum scores were derived by adding all items of clusters B-E (max 80). Participants will be instructed to answer in relation to an index trauma (dominant in intrusions) with 1-month time frame. The Patient Health Questionnaire (PHQ-9); [25]) will be used to measure depression severity. The nine-item questionnaire is to be scored from 0 (not at all) to 3 (nearly every day) according to the presence of the symptom in the previous two weeks. A sum score will be calculated for depression severity (max 27). To assess trauma-related dissociation, we will use the Shutdown Dissociation Scale (ShutD) [26]. This 13-item questionnaire assesses sensory deafferentation (e.g. transitory deafness or blindness), reduced nociception/analgesia, numbness, transitory paralysis, loss of speech/suppressed vocalisation, pseudo-neurological symptoms, (pre-) syncopes and out-of-body experiences on a 4-point scale (0—not at all to 3—several times a week). All items were added to a total score ranging from 0 to 39. Good psychometric properties were found in previous studies [35]. The Alcohol, Smoking and Substance Involvement Screening Test (ASSIST) [27, 36] will be applied to assess the risk of drug consumption for alcohol, cannabis and other recreational drugs; risk scores (‘low’, ‘moderate’ and ‘high’) indicate the probability of drug dependence as well as social, financial, health and legal problems consequent to the drug abuse. The Functionality will be assessed with the Work and Social Adjustment Scale (WSAS) [28]. Ongoing violence will be assessed by the scale Things I have seen and heard [29] and three additional questions asking whether the client has experienced any threat to physical or social integrity or was actively involved in violent perpetration. The applied instruments have successfully been used in various cultures with good psychometric outcomes (see e.g. [37] for PSSI-5; [38] and [39] for PHQ-9; [26] for ShutD; [36] for ASSIST; [40] for WSAS; [29] for Things I have seen and heard). Trained interviewers administer the questionnaires under close supervision in their first interviews until interviewing techniques and rating meets high standards. If possible, interviewers will do sit in to ensure interrater reliability.

### Plans to promote participant retention and complete follow-up {18b}

Follow-up data will be collected 3 and 6 months after treatment delivery. Patients who discontinued the trial will be provided care in the health centre.

### Data management {19}

Data will be stored and managed by Fiocruz during the active trial period (provision of treatments and follow up assessments) and transported to the University of Konstanz for later storage (10 years). To ensure data quality, entered questionnaires will be controlled. Before data analysis, we will also double check allocation of baseline and follow-up questionnaires via variables across time points and pursue further data quality checks (missings, invalid values, etc.). The data file will not include any information that would allow the identification of study participants. The final version of the data set will be shared via a private cloud server provided by the University of Konstanz which offers high security standards following e.g. ISO/IEC27001-2013 and offers a multi-layered encryption (e.g. via SSL/TLS, AES-256, end-to-end encryption).

### Confidentiality {27}

Pseudo-anonymisation, i.e. allocation of a code for each participant, is realised before the questionnaires are locked and archived in Fiocruz. A digital coding list combining the data secured with a 12-digit password is stored and updated regularly by the leading implementing personnel in charge. Questionnaires are entered in Fiocruz and missing values and inaccurate assessments are followed up. A data entry protocol is established and available upon request. Data integrity is further enforced before statistical analyses by checking validity of values and range.

### Plans for collection, laboratory evaluation and storage of biological specimens for genetic or molecular analysis in this trial/future use {33}

Not applicable as no biological specimen will be collected.

## Statistical methods

### Statistical methods for primary and secondary outcomes {20a}

To test the efficacy of NET in comparison to TAU in regard to primary (PTSD) and secondary (depression, shutdown dissociation, substance involvement, functionality) outcomes, we plan to use separate generalised linear mixed models (GLMMs) in R (R Core Team, 2018). To investigate the influence of ongoing violence, we will enter the sum scores for community and intimate partner violence as fixed model terms. To account for non-independence of measurements, we will include individuals as random model terms. To account for repeated measures, we will control the within-group variance for the effect of time, i.e. baseline and 3- and 6-month follow-ups, according to Field et al. [41]. To estimate the significance of the fixed terms, we plan to fit the models using maximum likelihood (ML) and compare models with and without each fixed term using likelihood-ratio tests (LRTs) [42]. In cases where interaction terms are significant, we will use post hoc Tukey tests using the R package emmeans [43] to assess which contrasts differ significantly. To correct for multiple comparisons controlling for the false discovery rate, we will adjust *P* values using the R built-in function p.adjust according to Benjamini and Hochberg [44]. Additionally, effect sizes will be estimated by calculating Cohen’s *d* [45] for within- and between-group differences. Clinically significant change will be calculated using the reliable change index, following Jacobson et al. [46] for clinical outcomes (PTSD, depression).

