## Introduction

### Background and rationale {6a}

About 114 million citizens of Brazil live in subnormal agglomerates (or *favelas*) [1]. These districts are characterised by social vulnerabilities such as lack of governmental services, poverty and high levels of violence [2]. About 35% of deaths by external causes in Brazil have been classified as homicides [3, 4]. In Rio de Janeiro particularly, the Western parts present with a high density of favelas. Here, the rate of homicides is about 10 times higher than in neighbourhoods of the South [5]. It is postulated that criminal organisations that are largely financed by trafficking of drugs and firearms play a major role in the escalation and the maintenance of high rates of violence [4]. The growing participation of children and youths is particularly alarming. The majority of individuals affected by urban violence are 25 years or younger [1]. According to a recent study by Ribeiro et al. [6], every third person in Rio de Janeiro had experienced a new traumatic event within 1 year. In the same sample, 87% reported at least one lifetime traumatic event [7]. Furthermore, insecurity and poverty affect familial relations and health [8]. In Brazil, the overall prevalence of intimate partner violence is estimated at about one third [9]. In a recent study, Serpeloni et al. [10] found that more than 50% of women who live in São Gonçalo city near Rio de Janeiro were exposed to intimate partner violence and 99% to community violence (e.g. witnessing fights, being threatened with a knife or a gun or witnessing killings). The risk of violence exposure remains high during pregnancy, a particularly sensitive period for mother and child. Common forms of violence are urban violence (60%), death of a close person (43%), accidents (34%), exposure to human remains (33%) or domestic violence (20%) [7]. About 71% of children reported hearing gunshots [7], 44% experience severe physical violence at home [11] and 22% of families experienced severe intimate partner physical violence [12]. In Brazilian women, mental health problems are particularly related to experiencing intimate partner violence [13]. Furthermore, family violence is a major determinant of mental health problems in children [12, 14]. Luz et al. [7] report an overall prevalence of 11% of posttraumatic stress disorder (PTSD) in Rio de Janeiro, assumedly with higher rates in low-income districts. Patients with PTSD have shown to be at a heightened risk for other mental disorders and also for experiencing more traumatic events. While subclinical tendencies of hypervigilance or avoidance may be adaptive at first, they substantially undermine the natural capacity to seek and avoid certain environments and intimate relationships. Evidence-based treatments for PTSD have been developed and tested [15]. Narrative Exposure Therapy (NET) [16] has emerged as an evidence-based treatment for patients in low- and middle-income countries and refugees, all of whom have been exposed to multiple traumatic stressors; for a review and meta-analysis, see Siehl et al. [17]. A substantial body of evidence shows the effectiveness of NET for patients who live in relatively safe conditions. Evidence is scarce however for circumstances of ongoing violence. Studies from post-conflict Eastern DR Congo with former combatants [18] and Iraqi women who live in a relationship with intimate partner violence [19] suggest beneficial but moderate effects so far.

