### Outcomes {12}

Outcomes will be measured 3 and 6 months after the treatment. PTSD symptoms will be assessed as primary outcome using the PTSD Symptom Scale Interview for DSM-5 [24]. The Patient Health Questionnaire [25] will be used to measure depression severity. To assess trauma-related dissociation, we will use the Shutdown Dissociation Scale [26]. Substance involvement will be evaluation with the Alcohol, Smoking and Substance Involvement Screening Test [27]. Functionality will be assessed with the Work and Social Adjustment Scale [28]. Ongoing violence will be assessed by the scale Things I’ve seen and heard [29] and three questions asking whether the client has experienced any threat to physical or social integrity or was actively involved in violent perpetration.

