### Methods for additional analyses (e.g. subgroup analyses) {20b}

Subgroup analysis might be considered for sex groups, level of violence exposure and/or perpetration.

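### The model that tests NET against TAU includes ongoing-violence scores not restricted to baseline, so its coefficient may not be the effect of being randomised to NET

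*Protocol article*

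**What the plan says.** All references are to the protocol article.

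- **Purpose of the models.** Statistical methods {20a} introduces separate generalised linear mixed models for each outcome with the aim "To test the efficacy of NET in comparison to TAU in regard to primary (PTSD" and secondary outcomes).
- **Violence terms.** The same paragraph continues: "To investigate the influence of ongoing violence", "we will enter the sum scores for community and intimate partner violence as fixed model terms". No time point is attached to the scores.
- **Testing.** Each fixed term is tested by a likelihood-ratio test that compares the model with and without that term. Measurements at baseline, 3 months and 6 months enter the model.
- **When violence is measured.** Outcomes {12} opens with "Outcomes will be measured 3 and 6 months after the treatment". Its list of measures ends with violence: "Ongoing violence will be assessed by the scale" Things I've seen and heard, together with "three questions asking whether the client has experienced any threat to physical or social integrity" or took an active part in violence.
- **Role of violence.** Sample size {14} calls the level of ongoing violence a covariate.
- **Randomisation.** Concealment mechanism {16b} places it after the baseline interview.
- **Link from PTSD to violence.** Background {6a} states: "Patients with PTSD have shown to be at a heightened risk for other mental disorders and also for experiencing more traumatic events". The Discussion adds that PTSD symptoms push social dynamics towards conflict and violent behaviour.

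**The concern.** Randomisation protects the comparison of the arms as allocated. It does not protect a comparison made at equal values of something that happened after allocation. If NET reduces PTSD, and PTSD raises the risk of new exposure or violent behaviour, follow-up violence may lie on the path from treatment to outcome. Holding it fixed then removes the part of the benefit that runs through violence. It can also bring in confounding from unmeasured causes shared by violence and PTSD. The scores are self-reported, so a treatment that works on trauma memory could also change what is reported.

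What is at stake is the trial's main question, whether NET is superior to TAU under ongoing violence. The protocol names no model-based NET test that avoids the issue.

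**Working it through.** **Step 1: is the NET test conditional on violence?** The likelihood-ratio test for a term drops that term and keeps the rest. With the violence scores among the fixed terms, the test of the NET terms is made with violence still in the model. The protocol names no alternative model for that test.

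**Step 2: are the scores post-randomisation?** The statistical section does not say. Four statements bear on it:

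- the construct is called ongoing violence in both {20a} and {14};
- {12} lists it with measures taken 3 and 6 months after treatment;
- {16b} puts randomisation after the baseline interview;
- the model contains baseline and follow-up rows, so the score is either a fixed T0 value or varies with time. In the second case the follow-up rows carry post-randomisation values.

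No statement restricts the scores to T0. The most plausible reading is that they are at least partly post-randomisation.

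**Step 3: how large could the effect be?** The protocol gives no figure to reproduce: it states no path from NET to violence and no numerical d. Every value below is therefore an assumption, in SD units.

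- a = reduction in violence caused by NET
- b = effect of violence on PTSD
- true total NET effect = 0.50

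In a simple regression of outcome on arm and follow-up violence:

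adjusted effect = total effect − a × b

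With an unmeasured cause of both violence and PTSD, path 0.3 to each, this becomes

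adjusted effect = total effect − a × (b + 0.3 × 0.3) = total effect − a × (b + 0.09)

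| a | b | a × b | Adjusted d | Adjusted d with shared cause |
|---|---|---|---|---|
| 0 | any | 0 | 0.50 | 0.50 |
| 0.2 | 0.2 | 0.04 | 0.46 (−8%) | 0.44 (−12%) |
| 0.3 | 0.3 | 0.09 | 0.41 (−18%) | 0.38 (−23%) |
| 0.4 | 0.4 | 0.16 | 0.34 (−32%) | 0.30 (−39%) |
| 0.5 | 0.5 | 0.25 | 0.25 (−50%) | 0.20 to 0.21 (−59%) |
| −0.3 | 0.3 | −0.09 | 0.59 (+18%) | 0.62 (+23%) |

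Simulation with 1,000,000 subjects per scenario agreed within 0.01 for every row except a = b = 0.4, which was not simulated and rests on the formula. Without violence in the model, the simulated effect was the true one to within the same margin. The last row is the case where NET raises exposure or its reporting, and the effect is then overstated. A shared cause acting in opposite directions on violence and PTSD would shift the last column the other way.

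For a true effect of 0.70, the same subtraction gives 0.70 − 0.04 = 0.66 at paths of 0.2, and 0.70 − 0.25 = 0.45 at paths of 0.5.

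**The case against.** The strongest reply is that the protocol never says the scores are taken after randomisation. The list in {12} also holds the PTSD interview, which is plainly given at T0 as well, so the list does not show that violence is measured only at follow-up. If only T0 scores enter the model, the problem disappears. This stands as a limit on certainty. It does not answer the point, because nothing restricts the scores to T0 and the wording leans the other way.

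Second, the path from NET to violence may be weak. Much community violence belongs to the district and lies outside a patient's control, and {6a} does not claim that treatment lowers exposure within six months. This also stands. The concern is stronger for intimate partner violence than for community violence.

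Third, {20a} also plans a between-group Cohen's d that is not said to be adjusted for violence. That is true, but it does not replace the model-based test.

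A reader might infer more than the documents support:

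- **That the NET estimate is biased.** This holds only if NET changes violence or its reporting.
- **That violence enters as a main effect only, so moderation cannot be seen.** {20a} provides for interaction terms without listing them, so an arm by violence term is not excluded.
- **That the violence subgroups share the fault.** {20b} says only "Subgroup analysis might be considered for sex groups, level of violence exposure and/or perpetration" and does not time the grouping variable.
- **That the trial would lose 8% to 32% of its effect.** Those percentages rest on assumed paths in a simpler model than the planned repeated-measures one.
- **That the intimate partner violence score has no source.** The article does not describe its derivation, but scoring detail may sit in the full protocol or the cited instrument.

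**Conclusion.** The point holds in conditional form. As written, the plan tests NET with ongoing violence in the model, does not confine those scores to baseline, and names no model-based NET test without them. On the most plausible reading, part of that adjustment is for something measured after randomisation that the protocol itself connects with PTSD.

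If NET alters violence or its reporting, the adjusted coefficient does not estimate the effect of being randomised to NET. If it alters neither, no bias arises from this source. Neither size nor direction can be settled from the documents. The loss of 0.04 to 0.16 in d is an illustration under assumed paths of 0.2 to 0.4 SD and should be quoted only as such.

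**What to change.** In Statistical methods {20a}:

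1. State that the primary NET versus TAU test comes from a model without post-randomisation violence. Adjust at most for violence measured at T0, if it is collected there.
2. Examine whether violence modifies the NET effect with an arm by T0-violence interaction.
3. Report the model containing follow-up violence as a labelled exploratory, mediation-type analysis.

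The question about the influence of ongoing violence is kept and moves out of the primary contrast. The cost is a change of analysis wording, a little extra analysis, and the loss of any precision that follow-up violence would have added to the primary model. If violence is not recorded at T0, the T0 adjustment and the interaction in item 2 are not available for patients already interviewed. Items 1 and 3 can still be carried out.

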### Interim analyses {21b}

No interim analyses will be conducted.

### Methods for additional analyses (e.g. subgroup analyses) {20b}

Subgroup analysis might be considered for sex groups, level of violence exposure and/or perpetration.

### Methods in analysis to handle protocol non-adherence and any statistical methods to handle missing data {20c}

All participants who provide reliable data at baseline will be recorded in the dataset and analysed as randomised. Furthermore, patients who die before the evaluation of efficacy outcomes (truncation due to death) are part of the principal analysis incorporating the timing of death of the trial participant.

Every effort will be made to prevent missing data. One of the advantages of GLMM over ANOVA is that the number of observations is maximised by excluding missing values only, rather than removing complete cases with some or all missing values present. In addition, imputation methods implemented in the mice R package [47] will be considered if more than 10% of the values in the whole dataset are missing and not more than 30% per participant per assessment instrument.

### Plans to give access to the full protocol, participant-level data and statistical code {31c}

Data as well as statistical codes will be available for the research team and shared for replication purposes upon request. Researchers with significant scientific contributions to the article will gain authorship. Participants will be informed throughout the baseline interview about the possibility to obtain information on the study outcome at their local health centre. A layman-friendly text on the study results will therefore be provided at the latter when publishing the results. In order to allow access to the study results to researchers in low- and middle-income countries, we will prioritise publication in journals that offer open access.

## Oversight and monitoring

### Composition of the coordinating centre and trial steering committee {5d}

Fiocruz is responsible for the coordination of activities on site (e.g. arrangements with the health centres, ensure availability of rooms, etc.) and ensure study implementation follows the study protocol. Interviewer and NET trainings are led by AK and FS and supervision is conducted by FS, JN and AK. Fiocruz with the support of the University of Konstanz is responsible for data management, which encompasses all tasks concerning processing and utilisation of study data, with the aim of guaranteeing high-quality data and providing a valid study database for statistical analyses. The University of Konstanz (SC) will be responsible for conducting statistical analysis and the publishing of data.

### Composition of the data monitoring committee, its role and reporting structure {21a}

A data monitoring committee is not warranted due to the minimal risk of the interventions/high level of evidence from other settings.

### Adverse event reporting and harms {22}

We expect a low frequency of SAEs caused by the NET itself. However, given the hostility of the environment, SAE will most likely be frequent. SAEs are events that (1) result in death, (2) are life-threatening, (3) require hospitalisation or cause prolongation of existing hospitalisation, (4) result in persistent or significant disability or incapability, (5) are a congenital anomaly or birth defect or (6) require intervention to prevent permanent impairment or damage (such as acute suicidality). SAEs will be monitored by the NET counsellors and interviewers. Together with their supervisor, they will decide which cases have to be followed up as SAEs and reported to the supervising clinical psychologist on site and the PI.

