### Intervention description {11a}

#### NET counsellors

Trained Brazilian health personnel (medical/family doctors, psychologists) and advanced psychology students will deliver NET under constant supervision by a NET expert.

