#### Narrative Exposure Therapy

NET will be delivered in 8–12 individual sessions of 90–120 min each in length by Brazilian NET therapists. The flexible number of sessions allows to test NET under naturalistic conditions and to adapt to the client’s trauma history. The initial session involves the construction of a lifeline whereby traumatic events are mapped out in chronological order and situated in the context of the patients’ lifetime period, as well as the wider systemic, and socio-political context at the time. A therapy plan is constructed according to the idiosyncratic experiences of the individual and traumatic events. In the subsequent exposure sessions, the most traumatic experiences are re-lived (emotional, sensory, cognitive, interoceptive) in order to transform the fragmented report of traumatic events into a coherent narrative. The therapist makes a written record of the event, and at the beginning of the next session, the narration is read to the patient and corrected for potential discrepancies. In the last session, the participant receives a written report of his/her biography.

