#### Treatment as usual

TAU receives (or continues to receive) the services of our collaborating health centre (where they have also been recruited from). The treatment is not standardised and typically targets the symptoms reported by the patient (often diagnosed as hypertension, depression, panic disorder). TAU includes pharmacotherapy, empathic listening, problem solving and practical or social support [23]. It does not include deliberate trauma exposure which is a key characteristic of evidence-based trauma therapy. Treatment doses will be assessed retrospectively during follow-up assessments.

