### Criteria for discontinuing or modifying allocated interventions {11b}

Study participation will be discontinued if a patient withdraws their written informed consent. In case of a serious adverse event (SAE), we will investigate a causal link between intervention and the occurrence of SAE and evaluate whether trial continuation would be a risk to the client, and whether modifications should be made to the intervention (e.g. support sessions). SAEs are defined as events that (1) result in death, (2) are life-threatening, (3) require hospitalisation or cause prolongation of existing hospitalisation, (4) result in persistent or significant disability or incapability, (5) are a congenital anomaly or birth defect or (6) require intervention to prevent permanent impairment or damage (such as acute suicidality). All SAEs that are reported by the patients will be evaluated by the clinical psychologist on site and the PI. Whenever a patient is withdrawn from the trial, the reasons for the withdrawal or treatment discontinuation together with the corresponding dates will be recorded. If a patient completely drops out from the study, a final examination will be conducted if possible. In particular, every effort will be taken to assess the primary outcome at follow-up. If a patient does not return for a scheduled visit, every effort will be made to contact the person to arrange further visits according to the protocol. Depending on the number of dropouts, missing values in primary outcome may either be excluded from the analysis or replaced according to the intention-to-treat principle or multiple imputation methods, respectively.

We expect that our sample of patients living in districts with high levels of urban violence may experience new traumatic events or death of family members, relatives or friends during the period of treatment. Patients will remain in the trial, but exposure sessions may be paused for few weeks. Support sessions may be provided according to the patient’s needs.

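### SAEs have more scheduled chances of detection in the NET arm and can be screened before the evaluators see them, so any comparison of SAE counts by arm risks ascertainment bias

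*Protocol article*

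**What the plan says.** All references are to the protocol article.

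- **Who monitors.** Adverse event reporting and harms {22}: "SAEs will be monitored by the NET counsellors and interviewers".
- **Who selects.** The same section continues: "Together with their supervisor, they will decide which cases have to be followed up as SAEs and reported" to the on-site clinical psychologist and the principal investigator.
- **Who evaluates.** Criteria for discontinuing or modifying allocated interventions {11b}: "All SAEs that are reported by the patients will be evaluated by the clinical psychologist on site and the PI". In that section an SAE leads to an inquiry into a causal link with the intervention and a judgement on whether continuing is a risk to the patient. Both sections give the same six-part SAE definition.
- **Contact in the NET arm.** Under NET counsellors {11a}, trained health personnel and "advanced psychology students will deliver NET under constant supervision by a NET expert". Under Narrative Exposure Therapy, "NET will be delivered in 8–12 individual sessions of 90–120 min each in length by Brazilian NET therapists".
- **Contact in the TAU arm.** Patients use the usual services of the health centres, and "Treatment doses will be assessed retrospectively during follow-up assessments". No SAE monitor is named for the treatment period.
- **Interviewers.** They are blinded (Who will be blinded {17a}). After randomisation they see both arms at T1 and T2 (Participant timeline {13}).
- **Oversight.** There is no data monitoring committee, on the ground of "minimal risk of the interventions/high level of evidence from other settings" ({21a}). Section {22} nevertheless expects SAEs to be frequent because of the setting.

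**The concern.** There are two separate problems.

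The first is unequal opportunity to detect. Staff who deliver one arm's treatment are also SAE monitors, and the other arm has no counterpart during treatment. If SAEs are as frequent as the article expects, the recurring question will be whether an event came from trauma-focused treatment or from the surroundings. The randomised control arm could help to answer that, but only if events are sought in the same way in both arms.

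The second is selection before review. Section {22} has monitors and their supervisor decide which cases go forward. Section {11b} has no such step for SAEs that patients report. A case held back would not reach the causality and continuation review, whether or not anyone ever compares the arms. Those deciding include staff who deliver NET and so know the allocation.

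**Working it through.** The article gives no SAE rate, no detection figure and no between-arm SAE analysis, so there is no stated figure to reproduce. The check is a count of contacts, a comparison of two sections, and an illustration with assumed values.

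**1. Scheduled contacts with a named SAE monitor after randomisation**

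- NET: 8 to 12 sessions plus 2 interviews (T1, T2). 8 + 2 = 10 and 12 + 2 = 14.
- TAU: 2 interviews.
- Ratio: 10 / 2 = 5 and 14 / 2 = 7.

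A TAU patient lost before T1 has no scheduled contact with a named monitor after randomisation. A NET patient lost at the same point may have had several.

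**2. The two SAE sections side by side**

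- {11b}: the patient reports an SAE, and the psychologist and principal investigator evaluate it, without exception.
- {22}: a monitor notices a case, the monitors and their supervisor decide whether it is followed up and reported, and only then do the psychologist and principal investigator see it.

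The evaluators and the definition are the same. The difference is the middle step. Composition of the coordinating centre {5d} names one set of supervisors and does not separate NET delivery from interviewing, so the supervisor's part is not shown to be independent of the NET team.

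**3. Illustration (all detection and risk values assumed)**

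Let p be the true SAE risk, equal in both arms; d the probability of detection; and f the probability that a detected case is forwarded. The recorded risk is p × d × f, so the recorded NET:TAU ratio is

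(d_NET × f_NET) / (d_TAU × f_TAU),

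and p cancels.

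With d_NET = 0.95 and equal forwarding:

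- d_TAU = 0.80: 0.95 / 0.80 = 1.19
- d_TAU = 0.60: 0.95 / 0.60 = 1.58
- d_TAU = 0.40: 0.95 / 0.40 = 2.375, about 2.4
- d_TAU = 0.95: ratio 1.00

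With the planned 30 per group and p = 0.20, the expected recorded count in NET is 30 × 0.20 × 0.95 = 5.7. In TAU it is 30 × 0.20 × 0.80 = 4.8, 30 × 0.20 × 0.60 = 3.6 or 30 × 0.20 × 0.40 = 2.4.

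Selective forwarding can cancel or reverse this. The ratio falls below 1 once f_NET / f_TAU drops below d_TAU / d_NET: 0.80 / 0.95 = 0.84, 0.60 / 0.95 = 0.63, or 0.40 / 0.95 = 0.42. The article gives no value for d or f, so neither size nor direction can be fixed.

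**The case against.** The other side has several fair points.

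- **TAU is not unmonitored.** A reader might infer that only counsellors watch for SAEs and that they see only NET patients. Section {22} names interviewers as well; they are blinded and see both arms. No sentence rules out contact between counsellors and TAU patients, or says that TAU patients can report events only at T1 and T2. What stands is narrower: the only in-treatment monitor the article names belongs to NET.
- **The sections need not contradict each other outright.** They can be read in sequence: staff decide whether a case is an SAE, and all SAEs are then evaluated. Some parts of the definition, such as whether an event was life-threatening, do need judgement. Even so, death and hospitalisation need little of it, and {22} speaks of deciding what is followed up and reported. The sequential reading still places the first judgement with monitors who include the treating staff.
- **The treating team does not decide alone.** The supervisor takes part, and interviewers are a second route. This softens the point but does not remove it, because no separation of supervisors is described.
- **No harms comparison is stated.** SAEs are not an endpoint, and the statistical section plans no test of them. That absence from an article is not a fault, and it would be wrong to say that a planned comparison is biased. The risk arises if counts by arm are set side by side.
- **A monitoring committee** would not by itself correct unequal detection, so its absence is context only.

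**Conclusion.** The point holds in limited form. As written, SAE ascertainment differs by arm: 10–14 scheduled contacts with a named monitor in NET against 2 in TAU. In addition, {22} adds a selection step that is in tension with {11b}. Any comparison of SAE counts by arm is at risk of ascertainment bias of unknown size and direction, and cases screened out would miss the causality review in {11b}. The ratios of about 1.2 to 2.4 rest wholly on assumed detection rates and equal forwarding. They show what unequal detection could do and do not predict what it will do. The contact count rests on the reading that counsellors have no SAE-monitoring role among TAU patients, which the article implies but does not state. The planned efficacy analysis is not affected. The wording should be corrected, and raw SAE counts by arm should not be compared without this caution.

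**What to change.** 1. Reconcile {11b} and {22}: every candidate event in either arm, however noticed, is logged and forwarded to the on-site clinical psychologist and the principal investigator, who judge whether it meets the six-part definition.
2. Ask both arms the same short set of SAE questions at T1 and T2, after the PSS-I, over the same recall window. The window needs a starting point common to both arms, because TAU has no defined end of treatment.
3. Base any between-arm comparison on those answers only, and list events first noticed in NET sessions separately.

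The cost is a wording change and a few questions at visits already planned. There will be more events to log, given the setting. The questions could lead a patient to reveal the allocation to the interviewer; asking them after the primary outcome limits that at the visit itself, but not for a later visit with the same interviewer. Recruitment began in October 2019, so interviews already completed would not be covered, and a report should say from when the common questions applied.
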